#### Blinding

The subjects will be blinded to the method used during their hospital stay. After hospitalization, blinding will become impossible to maintain reliably due to a nationwide medical database directly accessible to patients. The surgeon who will meet the patients at 10-month follow-up will not be the same as the operating physician and will be blinded to the method used. The radiologist will also be blinded to the method used.

### Data collection, management, and analysis

#### Data collection methods

All data will be collected prospectively on an electronic database designed for this study. The RAND-36 questionnaire to be used in this study has been well documented previously.

The reasons for withdrawal will be documented carefully. The investigator will attempt to contact the subject at least three times prior to designating them as lost to follow-up. The investigator will document the date and type of attempted communication. If a subject cannot be reached during the visit window, a missed visit will be recorded; after three consecutive missed visits, the subject will be considered lost to follow-up, and a study exit form will be completed in the eCRFs. Any data on subject participation and procedures until their withdrawal will be analyzed within the research.

#### Data management

All data will be handled with utmost confidentiality. Permission for the study register has been submitted to Oulu University Hospital, and a description of the register has been provided.

#### Data monitoring

There is no data monitoring committee named in this trial. All complications and harmful events will be carefully reported using specific eCRFs, and serious events will be reported to the principal investigator immediately. As previous studies on synthetic mesh in particular are scarce, a preliminary safety analysis at 30-day follow-up will be made on 20 patients on each group. Any serious concern raised at any point in the study on the safety of the meshes will result in the consideration of preliminarily aborting the study.

#### Statistical methods

The main endpoints are the presence (proportion) of stoma site incisional hernias with 95% confidence intervals for both groups at 10-month follow-up, and the incidence of surgical site infection at 30 days after the closure of the stoma. Secondary outcomes are the presence of stoma site incisional hernias at 3- and 5-year follow-up, the relative improvement to QoL during the follow-up, Clavien-Dindo classification of complications at 30 days postoperatively, operation time, length of hospital stay, and reoperation rate.

Between-group comparisons of continuous variables will be performed by Student’s *t* test or Mann-Whitney *U* test, the latter of which will be used if heterogeneous variances persist. Categorical data will be compared using χ^2^ or Fisher’s exact test. Repeatedly measured continuous data will be analyzed by a linear mixed model (LMM) using individuals as random effects. The covariance pattern for the LMM was chosen according to Akaike’s information criteria. Two-tailed *p* values will be reported. Analyses will be performed using SPSS (version 24 or higher) (IBM Corp., Armonk, NY, USA) for Windows and SAS (version 9.4 or higher) (SAS Institute, Cary, NC, USA).

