### Objectives

The objective of the Preloop trial is to compare synthetic mesh (Parietene Macro™, Medtronic) and biological implants (Permacol™, Medtronic) for the prevention of incisional site hernias after temporary loop-ileostomy closure (see Table 1). Our hypothesis is that synthetic mesh is equally safe and effective as biological implants in incisional site hernia prophylaxis, and that they both can significantly reduce the rate of incisional hernias detected in previous studies. Its lower price also makes synthetic mesh a more lucrative option. By demonstrating that synthetic mesh is equal to biological implants in terms of safety and efficiency, this study might encourage investigators to design upcoming trials that use synthetic materials in contaminated fields. As previous studies are scarce, the Preloop trial was planned as a pilot study to provide preliminary results on the safety and efficiency of both devices used in the study.

**Table 1 Tab1:** Comparison of devices in Preloop trial

Comparison of devices	Parietene Macro	Permacol
Manufacturer	Medtronic	Medtronic
Mesh type	Synthetic	Biological implant
Material	Macroporous monofilament polypropylene mesh	porcine dermal collagen implant
Size	Trimmed to fit retromuscular space, original size before trimming 10 × 15 cm	length 10 cm, width 5 cm

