#### Sample size

Two of the previously published retrospective studies reported the incidence of incisional hernias to be 13.5–21.5% on short-term follow-up after closure by suturing [8, 9]. Likewise, the number of hernias after closure with mesh has been very few in short-term follow-up [20, 22]. We assume that the hernia rate after closure by suturing detected in previous studies can be significantly diminished to about 5% with a prophylactic synthetic mesh or biological implant on long-term follow-up. The aim of the study is to generate preliminary results showing synthetic mesh is non-inferior to biological mesh. Assuming α = 0.05 and a power = 80% for incisional hernias and with 5% non-inferiority marginal, we would need 235 patients per group. Although previous studies on both biological implants and synthetic meshes have raised no concerns on the safety of the meshes [18–20, 22, 23], the use of synthetic meshes in contaminated surgical sites continues to be widely avoided in clinical practice, and no comparative studies on incisional hernia prophylaxis after temporary stoma closure exist. That said, we assume there is no difference in infectious complications between the meshes.

As this is a pilot study, each group will comprise 45 patients. Considering a possible 10% drop-out rate, our aim is to have 50 patients per group. Therefore, the estimated sample size of 50 in each group should give a reliable preliminary estimation of the safety and efficiency of both meshes for further studies.

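### The non-inferiority aim and its 5% hernia margin are not carried into the statistical methods, which plan only per-group confidence intervals and two-tailed tests of a difference

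*Protocol article*

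**What the plan says.** **Aim.** The Sample size section of the protocol article states: "The aim of the study is to generate preliminary results showing synthetic mesh is non-inferior to biological mesh". The Objectives section puts it as equality: "Our hypothesis is that synthetic mesh is equally safe and effective as biological implants in incisional site hernia prophylaxis". It then gives a motivation that opens "By demonstrating that synthetic mesh is equal to biological implants in terms of safety and efficiency" and goes on to the hope of encouraging later trials. The abstract's Discussion paragraph and the main Discussion also speak of equal safety, with effectiveness at least as good or equal.

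**Design figure.** "Assuming α = 0.05 and a power = 80% for incisional hernias and with 5% non-inferiority marginal, we would need 235 patients per group". This is the only place where a margin appears, and it concerns hernia only. For infection the section merely assumes no difference.

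**Actual size.** "As this is a pilot study, each group will comprise 45 patients", raised to 50 to allow for 10% drop-out.

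**Analysis.** The Statistical methods section says "The main endpoints are the presence (proportion) of stoma site incisional hernias with 95% confidence intervals for both groups at 10-month follow-up", with surgical site infection at 30 days as the other main endpoint. Categorical data go to a chi-square or Fisher's exact test, and "Two-tailed *p* values will be reported". The section gives no between-group difference with an interval, no comparison with the margin and no rule for non-inferiority.

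**The concern.** A chi-square or Fisher test takes no difference as its null hypothesis. Failing to reject that null does not show that synthetic mesh is at most 5 points worse, and in a small trial failure to reject is the likely outcome even when the difference is large. Two separate intervals, one per group, do not give the interval for the difference that a margin has to be compared with.

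The planned analysis therefore cannot address the stated aim. At stake is what can properly be said at the end about effectiveness, and about safety, where the only planned between-group comparison is again a test of difference. Later trials, which this pilot is meant to inform, would also lack the estimate they most need: the difference and its uncertainty.

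**Working it through.** **Inputs.** From the Sample size section: alpha 0.05 (sidedness not stated), power 80%, margin 5% (taken as absolute percentage points), 45 evaluable per group. Hernia rate 5% in both arms, from the expectation that the rate "can be significantly diminished to about 5% with a prophylactic synthetic mesh or biological implant on long-term follow-up"; using it at 10 months is an assumption.

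**1. The plan's own figure.** For non-inferiority of two proportions with no true difference:

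n per group = (z_alpha + z_power)² × 2p(1−p) / margin²

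Here 2 × 0.05 × 0.95 / 0.05² = 38.

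- One-sided 0.05: (1.645 + 0.842)² × 38 = 234.9, so 235. This matches.
- One-sided 0.025: (1.960 + 0.842)² × 38 = 298.3, so 299. This does not match.

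The design figure is thus a one-sided 0.05 non-inferiority calculation, which corresponds to a 90% two-sided interval for the difference. Drop-out: 45 / 0.90 = 50, which matches.

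**2. What the planned tests would show.** Probability of p ≥ 0.05 at 45 per arm, by exact enumeration over two binomial distributions (chi-square without continuity correction):

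| True hernia rate, synthetic vs biological | Fisher | Chi-square |
|---|---|---|
| 5% vs 5% | 99.4% | 95.1% |
| 10% vs 5% (exactly at the margin) | 94.3% | 83.8% |
| 15% vs 5% | 77.0% | 61.4% |
| 20% vs 5% | 52.0% | 37.4% |

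For infection the article gives no rates. With 20% vs 10%, assumed purely for illustration, the figures are 82.1% and 72.3%.

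**3. Single results** (synthetic vs biological; Newcombe 95% interval for the difference):

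- 8/45 vs 2/45: Fisher p = 0.090, not significant. The difference is 17.8 − 4.4 = 13.3 points (6/45), interval −0.1 to 27.3.
- 2/45 vs 2/45: p = 1.0, interval −10.9 to 10.9 points, so the margin is not excluded.
- 0/45 vs 0/45: p = 1.0, upper limit 7.9 points. At 90% it is z²/(n + z²) = 2.706/47.706 = 5.7 points, still above 5.

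**4. What a margin-based reading would deliver at 45 per arm**, both true rates 5%. Standard error = √(0.095/45) = 0.0459.

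| Interval | Half-width | Chance of meeting the criterion, normal approximation | Newcombe, exact enumeration |
|---|---|---|---|
| 90% (one-sided 0.05) | 1.645 × 0.0459 = 7.6 points | Φ(0.05/0.0459 − 1.645) = 28.9% | 20.7% |
| 95% (one-sided 0.025) | 1.960 × 0.0459 = 9.0 points | Φ(0.05/0.0459 − 1.960) = 19.2% | 11.8% |

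The expected half-width exceeds the margin at either level.

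**The case against.** **It is a pilot.** The article says so repeatedly, sets 235 aside openly, and describes the smaller sample as giving a preliminary estimate for further studies. For that purpose a proportion with an interval per group is a sensible output, and the sentence on categorical tests is generic. This stands in part: it excuses the low power, and the sample size is not the complaint. It does not remove the mismatch, because the Sample size section says that even the preliminary results are meant to show non-inferiority.

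**An unseen analysis plan may add the margin.** It may. But the article does not leave the analysis open: it names the estimate, the tests and the sidedness, and these conflict with its stated aim.

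**A reader might infer that the trial will take p > 0.05 as proof of equality.** The document does not say so. The Objectives sentence about demonstrating equality ends as a motivation for later trials, not as a decision rule. What is documented is that difference tests are the only between-group comparison of proportions offered.

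**A reader might also infer that every statement of the hypothesis carries the 5% margin, or that the missing infection margin is a separate error.** Only the Sample size section gives a margin, for hernia. A condensed article may leave an infection margin to the full protocol. It matters here only because an equal-safety claim could not be supported without one.

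**The fix does not rescue the question.** Correct: the criterion would seldom be met at 45 per arm. An interval for the difference shows that uncertainty, whereas a p-value can hide it. It is also too strong to say that a clearly worse mesh would almost always go undetected: at 20% vs 5%, Fisher's test is non-significant in about half of trials.

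**Conclusion.** The point holds as a conflict between two stated parts of the protocol article: a non-inferiority aim with a 5% hernia margin, and an analysis that never refers to the margin and tests a different hypothesis. A non-significant p-value must not be used to support equality, since at 45 per arm it is the likely result (Fisher 77%, chi-square 61%) even when hernias are three times as frequent.

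This rests on an absolute 5-point margin, 45 evaluable patients per arm, and a 5% rate in the biological arm at 10 months, although the article ties 5% to long-term follow-up. The infection figures use assumed rates and are illustrative only. The verdict does not say that the pilot is too small for its declared purpose, or that the investigators intend to equate non-significance with equality.

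**What to change.** In the Statistical methods section:

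1. For both main endpoints, make the synthetic-minus-biological risk difference with a score-type interval (Newcombe or Miettinen-Nurminen) the main between-group result. The per-group proportions with their intervals can stay.
2. For hernia, compare the upper limit with the 5-point margin at a level that matches the stated alpha: 90% for the one-sided 0.05 behind 235. If 95% is preferred, say so and restate 235 as about 299.
3. Report the infection difference as estimation only, and make no claim of equal safety from it unless a margin is set in advance.
4. State that p > 0.05 is not evidence of equality.
5. Present the results as pilot estimation, and say that with 5% true rates in both arms the hernia criterion would be met in only about 21% (90%) or 12% (95%) of trials with the Newcombe interval.

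The cost is a change of wording; no new patients or data are needed. The downside is that the reported conclusion will be less favourable than the stated hypothesis suggests.

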#### Closure of stoma site

The closure of the temporary loop ileostomy will be performed 2–4 months after uncomplicated anterior resection on subjects who had since received no adjuvant treatment. The re-establishment of intestinal continuity will be achieved through the ostomy trephine either by staples or by hand-sewn anastomosis, according to the surgeon’s preference, and the bowel will be positioned back into the peritoneal cavity. Midline laparotomy will be used in the case of extensive bowel adhesions. The posterior rectus sheath will be closed with interrupted 2.0 polydioxanone sutures (PDS Plus Antibacterial Suture, Ethicon, Johnson & Johnson, Somerville, NJ, USA). The retromuscular space will be dissected with monopolar diathermy or another suitable energy device to create the space for the mesh. In the first group, a biological implant measuring 10 cm in length and 5 cm in width with the corners slightly curved (Permacol™, Medtronic) will be placed in the retromuscular space established as described above. In the second group, a lightweight polypropylene mesh (Parietene Macro™, Medtronic) with measures matching the retromuscular space will be placed similarly into the retromuscular sublay position. Four interrupted 2.0 polydioxanone sutures (PDS Plus Antibacterial Suture, Ethicon, Johnson & Johnson), one in each corner of the mesh, will be used to fix the mesh to the underlying posterior rectus sheath. After mesh fixation, the anterior rectus sheath will be closed with interrupted 0 polydioxanone sutures (PDS Plus Antibacterial Suture, Ethicon, Johnson & Johnson). The skin defect will be closed by a running subcutaneous purse-string suture with a 2.0 polyglactin thread (Coated Vicryl Plus Antibacterial Polyglactin 910 Suture, Ethicon, Johnson & Johnson).

As a preoperative antibiotic, prophylaxis cefuroxime 1.5 g and metronidazole 500 mg administered intravenously (i.v.) will be used. Patients with a body mass index (BMI) ≥ 30 will receive cefuroxime 3 g and metronidazole 1 g i.v. If the patient has had a previous allergic reaction to primary prophylactic antibiotics, clindamysin 600 mg i.v. (or, in case of BMI ≥ 30, clindamysin 900 mg i.v.) and ciprofloxacin 400 mg i.v. will be administered. No mechanical bowel preparation will be given.

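### Operative time and length of stay are to be compared by unadjusted two-sample tests, which are valid but give up some precision that centre, BMI, ASA class and smoking could supply

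*Protocol article*

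**What the plan says.** All references are to the protocol article.

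- **Statistical methods.** For continuous outcomes, "Between-group comparisons of continuous variables will be performed by" the t test or, where variances are heterogeneous, the Mann-Whitney U test. For binary outcomes, "Categorical data will be compared using" χ² or Fisher's exact test. The only model is for repeated data: "Repeatedly measured continuous data will be analyzed by a linear mixed model (LMM) using individuals as random effects". No covariate is named.
- **Secondary endpoints.** Operative time in minutes and length of stay in days are both listed.
- **Pre-intervention data.** BMI, ASA classification and smoking history are collected before the stoma is closed.
- **Allocation.** Each centre has its own randomisation list, with blocks of two, four and six. No patient characteristic is used.
- **Sample size.** 45 patients per group, raised to 50 for 10% drop-out. The trial is called a pilot.
- **Main endpoints.** Both are binary: surgical site infection at 30 days, and "the presence (proportion) of stoma site incisional hernias with 95% confidence intervals for both groups at 10-month follow-up".

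**The concern.** The section does not leave the method open. It names the tests, and those tests exclude baseline terms. Operative time and length of stay may well vary with body size, ASA class, smoking and hospital, although the documents do not say by how much. A comparison that ignores these variables leaves whatever they explain in the error term. It also ignores centre, the one factor the randomisation controls, so precision gained by balancing centres is not reflected in the standard error.

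At stake is the width of the confidence intervals for two secondary outcomes in a trial of about 90 evaluable patients, whose purpose is to give preliminary estimates for later studies. The data needed are already being collected.

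**Working it through.** **1. The plan's own figures.** Evaluable patients: 45/(1 − 0.10) = 50 per group, as stated. The hernia calculation also reproduces. With 5% in each arm, a 5-point margin, one-sided α of 0.05 and 80% power, (1.645 + 0.842)² × 2 × 0.05 × 0.95/0.05² gives 235 per group. Neither figure concerns operative time or stay, but they fix the size (90 evaluable) and the assumed hernia rate.

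**2. Continuous outcomes.** Let R² be the share of outcome variance that the covariates explain. The documents do not give it, so it is an assumption shown over a range. With k covariates and N = 90, adjustment multiplies the variance of the mesh difference by about

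(1 − R²) × (1 + k/(N − k − 3)).

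The second factor is the cost of estimating the covariates. For BMI, ASA class and smoking as one term each, k = 3 and the factor is 1 + 3/84 = 1.036. The effective number per arm is 45 divided by the variance factor.

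| Assumed R² | Variance factor | SE ratio | 45 per arm acts like |
|---|---|---|---|
| 0 | 1.036 | 1.02 | 43 |
| 0.05 | 0.984 | 0.99 | 46 |
| 0.10 | 0.932 | 0.97 | 48 |
| 0.20 | 0.829 | 0.91 | 54 |
| 0.30 | 0.725 | 0.85 | 62 |

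Break-even is at R² = 1 − 1/1.036, about 3%.

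Centre adds five terms for the six hospitals listed under Study setting. The cost factor reflects chance imbalance between arms, and blocked lists within centre hold that imbalance small, so centre should add little. As a pessimistic bound, treat centre as not balanced at all: k = 8, factor 1 + 8/79 = 1.101, and 45 acts like 43, 45 and 51 at R² of 0.05, 0.10 and 0.20.

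**3. Hernia.** At the protocol's assumed rate, which "can be significantly diminished to about 5% with a prophylactic synthetic mesh or biological implant on long-term follow-up", 90 × 0.05 = 4.5 events are expected, or 1.5 per covariate with three covariates. A simulation with 45 per arm (4,000 runs per scenario; assumed covariate odds ratios 1, 1.5 and 2; assumed 30% ASA 3 and 25% smokers) gave adjusted-to-unadjusted variance ratios for the risk difference of 1.04, 1.03 and 1.00. A three-covariate logistic model failed to give finite estimates in about 40-53% of runs. There is nothing to gain.

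**4. Infection.** The protocol gives no infection rate. In the same simulation the variance ratios were 1.05, 1.01 and 0.97 at a 10% event rate, and 1.05, 0.98 and 0.95 at 20%. A separate simulation of a standardised risk difference (1,200 trials, 11-13% infection) cut the variance by 1.3% and 2.7%.

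**5. Chance imbalance.** With 45 per arm a standardised baseline difference has SD √(2/45) = 0.21. It exceeds 0.25 in size in 24% of trials for one covariate, and in 55% for at least one of three independent covariates. To see what that could do to infection, assume 25% have BMI of 30 or more, with infection risks of 20% v 8%:

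- SD of the imbalance: √(2 × 0.25 × 0.75/45) = 9.1 points, so a 95% range of ±17.9 points.
- Shift at the edge of that range: 17.9 × 0.12 = 2.1 points.
- Overall risk: 0.25 × 20% + 0.75 × 8% = 11%. SE of the difference: √(2 × 0.11 × 0.89/45) = 6.6 points.

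A near-worst imbalance therefore moves the infection result by about one-third of a standard error.

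**The case against.** The strongest reply is that nothing here is wrong. Unadjusted tests are valid after randomisation, and covariate lists are commonly left to an analysis plan, which is not shown. No R² is given, so the gain rests on an assumption. The cohort is also deliberately narrow: ASA 4-5 is excluded and the Discussion stresses homogeneity, so a large R² should not be presumed. No power claim or margin rests on operative time or stay.

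Most of this stands, and it limits the point to a suggestion. It does not remove it, because the section commits to tests that cannot adjust, and a better method is available from data already collected.

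Three stronger readings are tempting, and the documents do not support them:

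- A reader might infer that every single-time comparison, including the main endpoints, loses precision at no cost. Steps 3 and 4 show no gain for hernia and very little for infection. For continuous outcomes the gain is not free either, since below an R² of about 3% adjustment costs slightly more than it returns.
- A reader might infer that chance imbalance biases or invalidates the tests. The unadjusted standard error already allows for it, and type I error is not inflated.
- A reader might take the rule beginning "Patients with a body mass index (BMI) ≥ 30 will receive" as the protocol's statement that obesity is a separate risk group for the outcome. It is an antibiotic dosing rule and gives no infection risk by BMI.

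**Conclusion.** The point holds as a low-cost improvement for operative time and length of stay only. Under an assumed R² of 5-20%, the standard error falls by about 1-9%, and 45 per arm acts like about 46-54. This range counts the cost of three patient-level covariates and relies on blocked randomisation to keep the cost of centre small. With a lower R² there is little or no gain, and near zero there is a loss of about 2% in standard error. The planned tests remain valid, and the conclusions on hernia and infection are not affected.

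**What to change.** In Statistical methods, before unblinded data are seen, state for operative time and length of stay:

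- **Main comparison:** a linear model on mesh group, centre, BMI (continuous), ASA class and smoking, with robust standard errors, reporting the adjusted mean difference and its 95% CI. Robust standard errors also avoid switching between t and rank tests according to the observed variances.
- **Scale:** keep length of stay in days. The Outcomes section counts stay as a direct cost, for which mean days matter; a log scale would turn the comparison into a ratio.
- **Supporting result:** the unadjusted test now named.
- **Scope:** time to apply the mesh is recorded under Intervention data but is not a listed endpoint, so it need not be included.
- **Binary main endpoints:** leave hernia unadjusted. For infection, a risk difference standardised over one or two pre-stated covariates is an optional supporting analysis.

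The cost is a few sentences and no new data. The downside is a few degrees of freedom, and small centres may need pooling under a rule fixed in advance.

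### Unequal variances trigger a switch to Mann-Whitney U, which is the wrong remedy; the effect is small and limited to secondary continuous outcomes

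*Protocol article*

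**What the plan says.** Statistical methods in the protocol article gives one rule for single-measurement continuous data. "Between-group comparisons of continuous variables will be performed by" Student's t test or the Mann-Whitney U test, "the latter of which will be used if heterogeneous variances persist". Unequal variance is the only trigger named. Non-normality is not mentioned, and neither is a t test that allows unequal variances.

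The same section lists "operation time, length of hospital stay, and reoperation rate" among the secondary outcomes. The first two are continuous and fall under the rule. Quality of life does not: "Repeatedly measured continuous data will be analyzed by a linear mixed model (LMM". Both main endpoints are proportions. On sidedness the section says "Two-tailed *p* values will be reported". The Sample size section sets the evaluable number: "As this is a pilot study, each group will comprise 45 patients".

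**The concern.** The usual Mann-Whitney p value is derived for two identical distributions, which includes equal spread. When spreads differ, three things change:

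- The test addresses whether P(X<Y) = 1/2. That is not in general the same as equal means or equal medians.
- The variance used to standardise U is no longer its true variance, so the error rate can drift even when P(X<Y) is exactly 1/2.
- Because the switch depends on the observed variances, nobody knows before the data are in whether the reported result will concern a difference in means or a rank ordering.

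The rule therefore brings in Mann-Whitney in the situation where it is hardest to read as a comparison of location. Welch's t test, made for unequal variances, is not offered. At stake is how a p value for operating time or length of stay should be read.

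**Working it through.** **Inputs from the article.** 45 evaluable patients per arm (Sample size; 50 × 0.9 = 45), 1:1 allocation and two-sided tests. A nominal 5% level is used; the article states α = 0.05 only in the hernia calculation.

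**Inputs assumed.** The article gives no SDs or distribution shapes for operating time or length of stay, so SD ratios and shapes are varied over a range. It names no variance check either; the rule is modelled as Levene's test at p < 0.05, then Mann-Whitney, otherwise Student's t.

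**The plan's own figure.** The test-choice rule carries none. The only calculated figure is 235 per group for hernia. It reproduces with a 5% rate in both arms, a 5-point margin and one-sided α = 0.05: (1.645 + 0.842)² × 2 × 0.05 × 0.95 / 0.05² ≈ 235. It does not depend on the rule examined here.

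**Why the null variance is off.** With n per arm, the test uses Var(U) = n²(2n + 1)/12. At n = 45 this is 2025 × 91/12 = 15,356. Take symmetric data with a common centre and let one arm's spread become negligible beside the other's. U then depends only on how many of the wider arm's values lie above the centre, and Var(U) = n³/4 = 91,125/4 = 22,781. The ratio is 1.483 and its square root 1.218, so the nominal cut-off of 1.96 acts like 1.96/1.218 = 1.61, a rejection rate of about 11%. For symmetric data with equal arms, that is the limiting case.

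**Normal data, equal means and medians, 45/45 (40,000 simulated trials per row).**

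| SD ratio | Student | Welch | Mann-Whitney | Rule as modelled |
|---|---|---|---|---|
| 1.5 | 5.1% | 5.0% | 5.1% | 5.1% |
| 2 | 5.0% | 4.9% | 5.7% | 5.7% |
| 3 | 5.2% | 5.0% | 6.8% | 6.8% |
| 4 | 5.3% | 5.1% | 7.7% | 7.7% |

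A separate run gave about 5.3, 6.0, 6.7 and 7.9% for Mann-Whitney; the gaps are of the size expected from simulation error. With equal arms, Student's t tolerates unequal variance better than the test that replaces it.

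**Skewed data.** Take log-normal data with equal means and log-SD 0.3 versus 0.6.

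- Equal means force log-means of −0.3²/2 = −0.045 and −0.6²/2 = −0.18, a difference of −0.135.
- The medians then differ by a factor exp(−0.135) = 0.87, and P(X<Y) = Φ(−0.135/√(0.09 + 0.36)) = Φ(−0.20) = 0.42.
- Mann-Whitney rejects in about 26% of trials and the rule as modelled in about 19%. Student's t and Welch each reject in about 6%.
- With equal medians instead, the picture reverses: Mann-Whitney rejects in about 5.5% and Welch in about 17%.

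**How far Welch holds for means.** With log-normal data, equal means and log-SD 0.4 versus 0.6, 0.8 and 1.0, Welch rejects in 5.4, 6.8 and 8.6%. The rule as modelled rejects in 7.5, 32.7 and 65.0%.

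**The case against.** The strongest reply is about size and scope, and much of it stands.

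- **The 26% is not a plain false-positive rate.** A reader might infer that Mann-Whitney wrongly rejects in a quarter of trials. In that scenario the medians differ by about 13% and P(X<Y) is 0.42, so the test correctly rejects its own null. It is an error only if the mean is the target, and Statistical methods does not name the mean for operating time or length of stay. Mann-Whitney also stays valid for the null of identical distributions.
- **Three- or four-fold SD ratios are assumptions.** At a ratio of 1.5 the inflation is negligible. The article says that the two devices are placed by the same technique, which makes very different spreads in operating time hard to expect.
- **Unequal arms are unlikely to matter.** At 50 versus 40, with the larger SD in the smaller arm, Mann-Whitney reaches 9.1% at an SD ratio of 4. But allocation is 1:1 in small blocks, and both outcomes are recorded around the index admission, before most follow-up losses.
- **Harm from Student's t on skewed data is not shown.** A reader might infer it because skewness is not a trigger. At equal n, Student and Welch reject almost equally often in every scenario above.
- **Cost comparisons are not clearly reached.** Length of stay and operating room time feed the cost analysis, but Statistical methods names no test for costs.

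The word persist may point to an earlier step such as transformation. That would not change the finding, since the stated remedy for remaining heterogeneity is still Mann-Whitney. None of these points makes unequal variance a sound reason to use that test.

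**Conclusion.** The point holds as a minor one. The rule is stated in the article, not left to an unseen analysis plan, and its remedy is wrong for its trigger. With symmetric data and equal arms the cost is a rejection rate of roughly 5 to 8% over SD ratios of 1.5 to 4, where Welch stays at about 5%. With skewed data the main fault is that the question answered changes with the data; whether the resulting rejections are errors depends on an estimand that the article does not fix. These sizes rest on assumed SD ratios and shapes and on Levene's test as the variance check.

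A reader might infer that the trial's main conclusions are at risk. The article does not support that. Hernia and surgical site infection are proportions, repeated quality-of-life scores go to the mixed model, and the sample size does not use this rule. What is clearly reached is operating time and length of stay, both secondary, in a declared pilot.

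**What to change.** Delete the variance-triggered switch. Use Welch's t test for continuous outcomes measured once, reported as a mean difference with a 95% CI, with no preliminary variance test.

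For outcomes expected to be skewed, such as length of stay, fix the estimand and method before the data are seen:

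- a bootstrap CI for the mean difference where means matter, as for resource use; or
- a rank comparison valid under unequal spread, such as Brunner-Munzel, reported as an estimate of P(X<Y). It held at 5.0 to 5.1% in the normal scenarios tabulated above.

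**Cost.** The change takes a sentence or two. Welch's test is standard in SPSS and SAS. At equal n its statistic equals Student's and only the degrees of freedom change, from 88 at 45 per arm to no fewer than 44. The critical value thus moves from 1.99 to at most 2.02, so the power loss under equal variances is negligible. The downside is that Welch is mildly liberal for means under strong skew, about 6.5 to 9% in the more extreme cases, which is why length of stay needs its own prespecified method.
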